## Abstract

Sexual strangulation (also referred to as choking during sex) has become increasingly prevalent among young adults and disproportionately affects females. Epidemiological studies indicate that more than half of college-aged women report a lifetime history of being strangled during sex, and it is most often described as consensual. Despite its widespread occurrence, little is known about the acute and cumulative neurological consequences of this behavior. Pilot studies suggest associations between frequent sexual strangulation and elevations in blood biomarkers of neural injury, alterations in brain structure and connectivity, and increased mental health symptoms; however, existing evidence is limited by cross-sectional designs, short-term follow-ups, and small sample sizes. This prospective cohort study is designed to characterize both the acute and longitudinal neurological effects of sexual strangulation using multimodal assessments. A total of 200 young adult females (100 with frequent sexual strangulation exposure and 100 controls with no lifetime strangulation history), along with a pilot cohort of 40 males, will undergo comprehensive evaluations including blood-based biomarkers of neural injury and inflammation, multimodal MRI, cognitive and oculomotor testing, retinal imaging, and mental health assessments. Acute neurological responses will be assessed approximately 24 hours following a sexual event involving strangulation (or non-strangulation sex in controls), while longitudinal follow-up will occur every six months over 30 months to examine cumulative exposure effects. Semi-structured interviews conducted at each time point will characterize strangulation practices, contextual factors, consent dynamics, and associated symptoms. The primary objectives are to (1) examine baseline group differences in neurological health between individuals with frequent sexual strangulation exposure and non-strangulation controls, (2) identify acute neurological alterations following sexual strangulation, (3) determine associations between cumulative strangulation exposure and neural cellular, physiological, and functional integrity over time, and (4) characterize young adults’ experiences, contextual factors, and perceptions of sexual strangulation through semi-structured interviews. Collectively, this study aims to establish temporal relationships between sexual strangulation and neurological health outcomes and to inform clinical guidance, sexual health education, and harm-reduction strategies related to this increasingly common sexual practice.

## Introduction

Sexual strangulation, often referred to as choking during sex, has emerged as a common sexual practice among young adults [1–4]. Although frequently described as consensual, this behavior disproportionately affects females [5–7] and has become increasingly normalized through mainstream media, popular music, pornography, and social media [4,8–17]. Large-scale epidemiological surveys indicate that sexual strangulation is highly prevalent in college-aged populations, with more than half of young adult women reporting a lifetime history of being strangled during sex and a substantial proportion reporting repeated exposure [18,19]. Despite its widespread occurrence, sexual strangulation remains poorly understood from a neurological and physiological standpoint, and empirical data capable of informing clinical guidance or sexual health education are limited.

From a biological perspective, sexual strangulation involves external compression of the neck that can partially or fully obstruct cerebral blood flow, venous return, and/or airway passages [4,7]. These mechanisms can result in transient cerebral hypoxia and ischemia, physiological stress responses, and alterations in cerebral perfusion [20]. Acute symptoms commonly reported following strangulation include dizziness, visual disturbances, disorientation, and, in some cases, loss of consciousness [20]. Experimental and clinical literature from other contexts involving asphyxia or vascular compression, such as intimate partner violence, autoerotic asphyxiation, and certain martial arts practices, demonstrates that even brief episodes of cerebral hypoxia can disrupt neural cellular integrity, particularly in vulnerable brain regions such as the hippocampus and other subcortical structures [21–25].

Emerging pilot data suggest that sexual strangulation may be associated with both short-term and longer-term neurological alterations. Specifically, young adult females who have been strangled at least 4 times during sex in the past month showed higher levels of circulating S100B level [26], which is indicative of astroglial activation, increased cortical thickness in widespread brain regions [27], interhemispheric differences in neural activation patterns [28], and inefficient neural effort during working memory tasks compared to strangulation naïve controls [29]. Furthermore, a single event of being strangled during sex was also associated with acute impairments in ocular convergence, blunted positive effects of sexual activities on mental health [30], and elevations in several inflammatory cytokines and chemokines (e.g., CCL-2, VEGF-A) [31]. However, interpretation of these findings has been constrained by methodological limitations, including reliance on a cross-sectional design, smaller sample sizes, and limited ability to distinguish pre-existing differences from strangulation-related effects.

A critical gap is the absence of longitudinal, multimodal studies capable of characterizing neurological health at baseline, assessing acute responses following sexual strangulation, and tracking cumulative effects over time. Without such data, it remains unclear whether observed neurological differences reflect pre-existing vulnerabilities, transient brain responses, or progressive neural changes associated with repeated exposure. Additionally, little is known about how contextual variables, such as frequency, methods, perceived consent, and subjective experiences, may modify neurological outcomes.

To address these gaps, the present study employs a prospective cohort design integrating multimodal neuroimaging, blood-based biomarkers, cognitive and oculomotor assessments, retinal imaging, and semi-structured interviews. This approach is designed to (1) examine baseline neurological differences between individuals with frequent sexual strangulation exposure and non-strangulation controls, (2) characterize acute neurological responses following sexual strangulation, (3) evaluate associations between cumulative exposure and neural cellular, physiological, and functional integrity over time, and (4) characterize participants’ experiences, perceptions, and behaviors related to sexual strangulation. By establishing temporal relationships and integrating biological and behavioral data, this study aims to generate critical evidence to inform clinical awareness, sexual health education, and harm-reduction strategies related to this increasingly common sexual practice.

### Aims and hypothesis

The aim of this study is to characterize baseline, acute, and longitudinal brain health associated with sexual strangulation in young adults using multimodal neurobiological, cognitive, and behavioral assessments.

### Specific aims

Aim 1 To examine potential group differences at baseline in neurological health between the strangulation and control groups through comprehensive neurological measures.Hypotheses: (1a) Significant differences in brain activation patterns and neuronal connectivity, increases in blood biomarkers for astrogliosis, inflammation, and axonal microstructural injury, alteration in retinal integrity, and declines in cognitive, ocular-motor, and mental health function will be observed in the strangulation group compared to controls. (1b) We will explore potential mediating factors, including behavioral, history, and broader demographic factors, driving group differences in neurological health.Aim 2: To identify the acute neurological effects of sexual strangulation through the response profile of multimodal neuroimaging, blood biomarkers, cognitive and mental health assessments, and visual health assessments.Hypotheses: (2a) Within the strangulation group, significant alterations in brain activation patterns and neuronal connectivity, increases in blood biomarkers for astrogliosis, inflammation, and axonal microstructural injury, alteration in retinal integrity, and declines in cognitive, ocular-motor, and mental health function will be observed acutely (~24h) after being strangled during sex compared with baseline. (2b) The control group will have no worsening of neurological outcomes, resulting in a significant group difference at a post-acute time point. Also, individual cerebral hemodynamics via perfusion measure and fMRI activation patterns in risk and reward pathways will be explored in response to acute sexual strangulation events.Aim 3 To determine the associations between cumulative exposure to sexual strangulation and neural cellular, physiological, and functional integrities.Hypotheses: (3a) Frequent sexual strangulation will correlate with negative neurological outcomes, and this association will strengthen over time. (3b) The neurological impact of cumulative strangulation will be pronounced in blood biomarkers, indicative of astrogliosis, inflammation, and reduced axonal microstructural integrity, surface and subcortical morphology, neural activation patterns in the limbic regions, and cognitive function. (3c) Cumulative effects of sexual strangulation will also be captured through a series of mental health and visual health assessments. For those switching their sexual behavior (e.g., controls who report new onset of strangulation experiences), an exploration of how brain health changes as they initiate or cease engaging in sexual strangulation will be conducted.Aim 4: To examine longitudinal characteristics, perceptions, and experiences of sexual strangulation via semi-structured interviews.Semi-structured interviews in connection with each laboratory visit will address how one’s experiences with sexual strangulation change over time in terms of frequency, duration, methods of strangulation, consenting status, motivations, and associated symptoms. These data will not only play a crucial role in informing behavioral targets for educational guidelines and interventions, but also identify behavioral patterns and contextual factors that modify neurological outcomes. For example, our exploratory analysis will examine the role of alteration in consciousness (AIC), such as visual changes, disorientation, loss of consciousness, or dizziness) on neurological outcomes by comparing AIC and non-AIC subgroups.Exploratory Aim 5: To examine neurological implications of sexual strangulation among a pilot cohort of males.Since no neurological data related to sexual strangulation exist for males, pilot cohorts of males (n=20 per group) will be included to generate preliminary data and hypotheses for future research.Exploratory Aim 6: To explore various contextual and modulatory factors that are influencing neurological and psychological wellbeing over time in relation to sexual strangulation and non-strangulation related sex.Leveraging comprehensive assessments of participants’ demographics, prior sexual history, and contextual factors (e.g., menstrual cycle, birth control, sleep, substance/tobacco/alcohol use), we will explore how these factors contribute to individual responses to sexual strangulation and general sexual activities. This aim will include exploration of those who switch sexual behavior (e.g., stopping strangulation or control starting to engage in strangulation).

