## Methods

### Participants

This prospective cohort study will enroll a total of 240 young adults, including 200 females and a pilot cohort of 40 males. Female participants will be assigned to one of two primary groups: individuals with frequent exposure (≥4 times per month) to sexual strangulation (n = 100) and age-matched controls with no lifetime history of being strangled during sex (n = 100). An additional pilot cohort of males (n = 20 per group) will be recruited to generate preliminary data on neurological correlates of sexual strangulation in males. The recruitment is anticipated to start in late February 2026 until March 2029, and all data collection is expected to finish by May 2030. Primary analyses will finish by May 2031. Eligible participants will be between 18 and 26 years of age and recruited primarily from the Indiana University campuses and surrounding community. Longitudinal follow-up of enrolled participants will extend up to 30 months. All participants will provide electronic written informed consent prior to enrollment. The initial study protocol has been approved by the Indiana University Institutional Review Board (#27400) on Jun 04, 2025. Upon completion of primary and secondary analyses, all relevant data will be made publicly available in sites including *brainlife* and inter-university Consortium for Political and Social Research (ICPSR).

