#### Baseline assessment.

Between enrollment and the baseline laboratory visit, participants will complete a series of online questionnaires assessing demographics, medical and neurological history, sexual behavior history, and Adverse Childhood Experiences (ACES). At the baseline visit, participants will undergo various assessments, including testing day questionnaires to gauge various contextual information (menstrual cycle, exercise), capillary blood sampling to test blood fatty acid components, urinalysis to verify pregnancy status, blood sampling for biomarker analysis, MRI, cognitive testing, oculomotor assessments, retinal imaging, and mental health questionnaires. Baseline assessments are designed to characterize neurological health prior to acute or longitudinal exposure assessment and to allow examination of baseline group differences between participants with frequent sexual strangulation exposure and non-strangulation controls. The baseline visit will end with setting up a MyCap account within Research Electronic Data Capture (REDCap) for participants for acute visit purposes. Participants in both the strangulation group and control group will participate in the acute aim (aim 2), but control participants who are not sexually active will not be participating in the acute aim.

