### Statistical analyses

#### Baseline group analysis.

To test whether neurological outcomes differ at baseline between the strangulation and control groups, we will use multivariable regression models with each baseline neurological outcome as the dependent variable and group (strangulation vs control) as the primary independent variable. For continuous outcomes (e.g., biomarker concentrations, imaging metrics, cognitive scores, NPC distance, OCT measures), we will use linear regression (or generalized linear models with appropriate functions if distributional assumptions are not met). For binary outcomes (e.g., presence/absence of symptoms or threshold-defined impairment), we will use logistic regression. Models will adjust for prespecified baseline covariates that are clinically relevant and/or imbalanced between groups, including age, BMI, prior concussion history, and baseline mental health symptoms. Because baseline neural health may be influenced by contextual factors, we will additionally consider time since last sexual event, substance use, sleep, and ovarian hormone levels/menstrual cycle phase as covariates when relevant to specific outcomes. For imaging outcomes, scanner-related and acquisition covariates (e.g., motion indices) will be included as standard quality-control adjustments. We will control for multiple comparisons using a false discovery rate (FDR) approach within each modality (biomarkers, imaging, ocular/retinal, cognition, mental health). As a complementary approach that leverages correlation among outcomes, we will conduct multivariate testing within domains (e.g., principal-component-based composite scores) to evaluate whether a domain shows an overall baseline difference by group prior to interpreting individual endpoints. Where appropriate, we also may consider exploratory mediation and explanatory models to help explain baseline group differences. We will use mediation analyses to estimate indirect effects while adjusting for confounders.

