### Sample size

Sample size estimates were based on power calculations using pilot data and related literature. Pilot data demonstrated moderate to large effect sizes across blood biomarkers (Cohen’s d = 0.52–0.87), resting-state functional connectivity (d ≥ 1.2), and cortical morphology (d = 1.4–2.9). Using a conservative estimate of a moderate effect size (d = 0.60), an alpha level of 0.01 to account for multiple models, and a repeated-measures design, a sample of 60 females per group will provide 80% power to detect within-group acute changes and group-by-time differences. An additional pilot sample of 10 males per group will be included to generate preliminary effect-size estimates. For the cumulative longitudinal analyses, power calculations were informed by pilot data and evidence from related hypoxic and subconcussive injury models demonstrating moderate to large effects. Assuming a conservative effect size of d = 0.50, an alpha level of 0.01, and a worst-case dropout or group-switching rate of 20%, a total of 200 females (n = 100 per group) will provide greater than 80% power to detect group differences and longitudinal exposure-response effects over 30 months. To support hypothesis generation for future studies, an additional pilot cohort of 20 males per group will be included.

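### Hypothesis 1b lists history and demographic factors as mediators; for those that precede exposure an indirect effect of strangulation is undefined, and confounding would be labelled as one

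*Protocol article*

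**What the plan says.** The protocol article, Specific aims, hypothesis 1b: "We will explore potential mediating factors, including behavioral, history, and broader demographic factors, driving group differences in neurological health". The last two sentences of Baseline group analysis turn this into a method. The first sets its status: "Where appropriate, we also may consider exploratory mediation and explanatory models to help explain baseline group differences". The second names the quantity: "We will use mediation analyses to estimate indirect effects while adjusting for confounders".

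Earlier in the same section the primary baseline regressions adjust for prespecified covariates, "including age, BMI, prior concussion history, and baseline mental health symptoms". Baseline assessment lists what the questionnaires collect before the first laboratory visit: "demographics, medical and neurological history, sexual behavior history, and Adverse Childhood Experiences (ACES").

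No section limits the candidate mediators to factors that can arise after strangulation has begun. The Introduction gives the difficulty of separating pre-existing differences from effects of strangulation as a limitation of the pilot work.

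**The concern.** An indirect effect is the part of an exposure's effect that passes through a variable which the exposure changes. Strangulation in young adulthood cannot change a participant's demographic background, her childhood adversity, or any event dated before she was first strangled. For such a factor there is no pathway to estimate. What the calculation returns is the product of two associations, group with factor and factor with outcome, and a factor with both associations is a confounder.

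Adjusting for confounders inside the mediation model does not solve this, because the factor placed in the mediator position is not itself adjusted away. Its contribution is split off and labelled an indirect effect. A pre-existing difference between the groups would then carry the label of an effect of exposure, on the question that the Introduction says earlier work could not answer.

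**Working it through.** **Plan's own figure.** None is given for the mediation analysis. The alpha of 0.01 under Sample size belongs to the acute and longitudinal calculations, so results are shown at both 5% and 1%.

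**What the product estimates.** Let C be a pre-exposure factor and Y an outcome, both with within-group SD 1. Write a for the group difference in C, b for the coefficient of C in a regression of Y on group and C, and c′ for the group coefficient in that regression. The unadjusted group difference in Y is c = c′ + a·b. If strangulation has no effect and C is the only source of difference, c′ = 0 and c = a·b. The so-called indirect effect is then exactly the confounding bias. For a = 0.5 and b = 0.3 it is 0.5 × 0.3 = 0.15 SD; the simulated mean was 0.149.

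**Simulation inputs.** From the protocol (Participants): 100 females per group. Assumed, because the protocol gives no values: a from 0 to 0.8 SD, b from 0 to 0.5. Group has no effect on C or Y. There were 4,000 runs per row, with two-sided tests. The joint test requires both paths to be significant; the Sobel test divides a·b by its delta-method standard error.

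| a (SD) | b | Joint, 5% | Sobel, 5% | Joint, 1% | Sobel, 1% | a·b (SD) |
|---|---|---|---|---|---|---|
| 0 | 0.3 | 5% | 3% | 1% | <1% | 0 |
| 0.5 | 0 | 4% | 1% | <1% | 0% | 0 |
| 0.2 | 0.2 | 24% | 10% | 7% | 1% | 0.04 |
| 0.3 | 0.3 | 55% | 43% | 29% | 13% | 0.09 |
| 0.5 | 0.3 | 93% | 88% | 78% | 55% | 0.15 |
| 0.5 | 0.5 | 95% | 94% | 83% | 80% | 0.25 |
| 0.8 | 0.3 | 99% | 99% | 96% | 91% | 0.24 |

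**Hand check of two joint-test rows (normal approximation, 5%).** Path a has z = a/√(2/100). Path b has z = b/√(1 − b²) × √200.
- a = 0.5, b = 0.3: z = 0.5/0.1414 = 3.54, power Φ(3.54 − 1.96) = 0.94; z = 0.3145 × 14.14 = 4.45, power Φ(2.49) = 0.99. Product 0.94 × 0.99 ≈ 0.93.
- a = 0.2, b = 0.2: z = 1.41, power Φ(−0.55) ≈ 0.29; z = 0.2041 × 14.14 = 2.89, power Φ(0.93) ≈ 0.82. Product ≈ 0.24.

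**With C moved to the covariates.** The adjusted group effect was significant in 4.2% to 5.3% of runs at 5% and 0.8% to 1.1% at 1%, which is nominal. A second variable M, which group does not affect but which depends on C (coefficient 0.5), was wrongly declared a mediator in 25% to 44% of runs when C was left out, and in 0.1% to 0.3% when C was a covariate (joint test, 5%; a and b of 0.5 and 0.3, 0.5 and 0.5, 0.8 and 0.3).

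**The case against.** The strongest reply is that little rests on this analysis. It is exploratory and conditional on being appropriate, and it sits beside unspecified explanatory models to which demographics and childhood history might be assigned. The main baseline comparison is a covariate-adjusted regression. The Discussion states that the observational design does not permit causal inference. Hypothesis 1b can be read as asking what accounts for the group gap, pre-existing history included. A list of mediators by variable could well sit in an analysis plan that is not shown. All of this lowers the weight of the point. It does not make an indirect effect through a pre-exposure factor meaningful, and if the intent is only to explain the gap, the method named is the wrong one. The rewording is the same either way.

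Three further objections stand and limit the claim.
- Not all history precedes exposure. Medical, neurological and sexual history is collected from participants already exposed at baseline, so some of it may follow first strangulation and could be a genuine mediator. Behavioral factors may be too.
- A reader might infer that the same variables are planned as both mediators and confounders. The text shows this only for classes of factor: age is demographic and prior concussion is history, but 1b names no individual variable and does not name childhood adversity.
- A reader might infer that the investigators will report such results as a mechanism of harm. No section says so.

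It is also fair that the simulation builds in a real confounder and then detects it. That is its purpose: it shows how often the analysis would attach the wrong label, not how common such factors are. Controls are age-matched, so age itself should contribute little.

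**Conclusion.** The point holds in a conditional form. As worded, 1b together with the planned indirect effects admits mediators that exposure cannot influence, and for these the estimand is undefined. Childhood adversity is taken here to precede first strangulation.

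A reader might infer that the test will be significant whenever strangulation has no effect. That is too strong. Rejection exceeds alpha only when the factor both differs between groups and predicts the outcome. The excess is modest for small values, particularly with Sobel or at 1%, and large for moderate ones. The rates depend on assumed associations, since the protocol supplies none. The identity between the estimate and the confounding bias does not depend on the values chosen.

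Because the analysis is exploratory and optional, no primary conclusion is at risk. The correction is still worth making, since it decides whether a pre-existing difference is reported as confounding or as an effect of exposure.

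**What to change.** Reword hypothesis 1b and the last two sentences of Baseline group analysis along these lines: demographic factors, childhood adversity and history dated before first strangulation will be treated as potential confounders; the group difference will be reported before and after adjustment for them, and the change described as confounding, not as an indirect effect; exploratory mediation will be limited to factors that arise after first exposure. The interviews already ask about onset of strangulation, which helps to date history items.

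Give each variable one stated role per model. Sleep and mental health symptoms need this most: both are primary outcomes in Table 1, baseline mental health symptoms are a covariate in the baseline model, and sleep is a possible one.

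Where mediation is pursued, the six-monthly visits can supply the time order, with exposure at one visit, mediator at the next and outcome at a later one. This should be labelled an exploratory longitudinal analysis, because it answers a different question from the baseline comparison in Aim 1.

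The cost is a few sentences of wording and some work to assign roles. No new data are needed. The small downside is that fewer participants will have the later visits.
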